### Participants

The following inclusion criteria will be used to select eligible patients for participation in the study:

• The patient is acutely admitted to the surgical ward with a hip fracture during the research period;

• The patient is not admitted with polytrauma;

• The hip fracture is not a pathological fracture;

• The patient is 65 years of age or older;

• The patient will be operated on the hip fracture;

• The patient does not participate in an interfering study;

• The patient is in a good cognitive condition to fully understand the information about the study and to give Informed Consent.

Patients will be recruited as quickly as possible after admission to the hospital. The patients will be included by the nurses working in de wards, this process will be closely monitored by the researchers. When a patient is eligible for participation the study will be explained to them and Informed Consent will be asked. If the inclusion by the nurses does not work out as intended, the researchers will have to take over this part of the data collection.

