### Blinding

In this trial blinding of the patients is not possible as they either do or do not receive the material belonging to the interventions, and are therefore automatically aware of the intervention group. Since the physicians will not be directly involved in the inclusion of patients they are unaware of the intervention group a patients belongs to. For the assessment of the outcomes during a telephone interview two weeks after discharge the interviewer will be aware of the intervention group a patient belongs to because specific additional questions for each intervention group will be asked to evaluate the interventions. However, the interviewer will not be informed about the background, research questions and outcome measures of this study. For the telephone interview six months after discharge the interviewer will be unaware of the intervention group that the patient belongs to. Finally, the reviewers in the retrospective record review study will be blinded, they will assess some of the outcome measures and should therefore be unaware of the interventions that a patient might or might not have received to prevent possible biases in their assessment.

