#### Method

The incidence of complications and AEs will be measured within the care chain and especially during the hospital admission of elderly hip fracture patients. In this study we look at the care chain from the moment that the patient is brought into the emergency department until six months after discharge from the hospital. Therefore the patients' hospital record will be studied in retrospect by an experienced surgeon. For the baseline measurement patient records of hip fracture patients acutely admitted in 2007, the year previous to the start of the intervention study, will be reviewed using a structured review form. In each hospital all surgical and orthopaedic admissions of patients with a hip fracture of 65 years or older will be selected. Of these selected index admissions the medical, nursing and, if existing, the outpatient records will be collected, the X-rays made during the admission will also be available. Records of patients with a pathological fracture, polytrauma or elective admission will be excluded. The main outcome variables in this part of the study are: rate of complications, adverse events, near misses and information transfer between care providers.

The patient records will be reviewed by a team of eight experienced reviewers. The selection criteria for the reviewers are:

• At least ten years post graduate clinical (surgical) experience;

• Surgical experience with hip fractures;

• Good reputation among colleagues;

• No longer than 8 years retired at the start of the study;

• Experience or affinity with analysis of incidents, complaints and errors.

Most of the reviewers have participated in a previous record review study [39] and therefore are already familiar with this type of research, terminology and methodology. Nevertheless, they will all follow a half-day training led by the research team and one experienced reviewer. During this training, the definitions, study protocol, adjusted review form and examples of AEs will be discussed. The reviewers will also receive a review manual. They will be compensated for their review activities at an hourly rate for expenses. During the review process the reviewers can ask advice from a general internist about accepted clinical practice in the specialty of internal medicine.

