##### Implementation

Within the research programme, half of the included patients in the intervention wards will receive the patient safety card. The card will be given to the patients during the hospital admission with a short instruction on how to use the card.

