##### Evaluation

The implementation and effectiveness of the patient safety card will be established during an interview by telephone with the patient two weeks after discharge. We will consider the patient safety card successful when 60% of the patients has used the card and found it useful. One of the topics in the interview is therefore about the use and possible added value of the patient safety card and the need and possibility for patients and their family to get actively involved. Also, the possible consequences of the use of the patient safety card on the patients' trust in health care are discussed during these interviews. Finally, during the retrospective patient record review six months after discharge the number of complications and adverse events will be determined and compared to the baseline measurement.

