##### Implementation

In the intervention wards 50% of the included patients will receive the leaflet with instructions. For each included patient a short questionnaire about the health status before discharge will be filled out to determine for which complications a patient may be at increased risk. The chapters concerning these complications are checked in the leaflet to indicate the most relevant information for each specific patient.

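### The card's effect on complications is to be compared with 2007 records, which cannot isolate the card; the randomised card v no-card contrast is available but not named

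*Protocol article*

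**What the plan says.** **Comparator for the card.** Intervention B, Evaluation, ends with the record review six months after discharge, at which "the number of complications and adverse events will be determined and compared to the baseline measurement".

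**What the baseline is.** Baseline measurement, Method, describes a retrospective review of "patient records of hip fracture patients acutely admitted in 2007, the year previous to the start of the intervention study". On selection: "In each hospital all surgical and orthopaedic admissions of patients with a hip fracture of 65 years or older will be selected". Pathological fractures, polytrauma and elective admissions are excluded.

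**Who enters the trial.** Participants applies those exclusions but also requires planned surgery, consent and adequate cognition: "The patient is in a good cognitive condition to fully understand the information about the study and to give Informed Consent".

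**What is randomised.** Study design and Randomisation allocate individual patients within the three intervention wards, in equal numbers, to SBAR alone (group 1), SBAR plus card (2), SBAR plus leaflet (3) or all three (4). SBAR is not randomised and covers all patients in those wards. Intervention B, Implementation, says that "half of the included patients in the intervention wards will receive the patient safety card". For the leaflet, Intervention C, Implementation, says: "In the intervention wards 50% of the included patients will receive the leaflet with instructions".

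**Other comparators.** Study design gives usual care, which is one ward in another hospital. General data collection and follow up uses the second record review for the programme as a whole. Intervention C, Evaluation, names no comparator for the leaflet. Data analysis promises intention to treat and analyses at patient and group level, without naming a contrast.

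**Trust.** Question 2b concerns error signalling and trust. Intervention B, Evaluation, says that "the possible consequences of the use of the patient safety card on the patients' trust in health care are discussed during these interviews". Blinding adds that at two weeks "specific additional questions for each intervention group will be asked to evaluate the interventions".

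**The concern.** A difference between card patients and 2007 patients has at least four possible causes besides the card: SBAR, the leaflet in half of the card patients, changes in care over time, and a different case mix. The case-mix difference has a likely direction. The article's own limitations section says that leaving out patients with dementia may make problems look less frequent in the trial. A fall in complications since 2007 could therefore appear with no card effect at all.

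Patients in the same wards and the same period, all under SBAR, are already being randomised to card or no card. If the report follows the sentence in Intervention B, a before-after difference may be credited to the card while the randomised answer goes unreported. Trust faces a related problem: if only card holders are asked about it, question 2b has no comparison group.

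**Working it through.** **1. The plan's own figure.** Inputs from Power calculation: 5-point reduction, SD 10 points, alpha 0.05, power 80%.

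n per group = 2 x (1.960 + 0.842)² x (10/5)² = 62.8, so 63. The t-test version gives 63.8, so 64, as stated (two-sided; a one-sided test would give 50). Then 64/0.80 = 80 per group, and 4 x 80 = 320. The enrolment figure therefore allows for 20% loss.

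**2. What each comparison contains.**

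| Source of difference | Card patients v 2007 | Groups 2+4 v 1+3 |
|---|---|---|
| Card | yes | yes |
| SBAR | yes | no, both sides have it |
| Leaflet | yes, 80 of 160 card patients | no, 80 of 160 on each side |
| Calendar time | yes | no, concurrent |
| Consent, cognition, surgery criteria | yes, not stated for 2007 | no, same criteria |

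**3. How misleading the 2007 comparison could be.** This is an illustration; the article gives no complication rate. Assumptions: 300 baseline records, 160 card patients, no card effect, baseline risk 20% to 50%, two-sided 5% test of two proportions.

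Worked case, 30% falling to 25% for other reasons:
- pooled risk = (160 x 0.25 + 300 x 0.30)/460 = 0.283
- null SE = √(0.283 x 0.717 x (1/160 + 1/300)) = 0.0441
- alternative SE = √(0.25 x 0.75/160 + 0.30 x 0.70/300) = 0.0433
- z = (0.05 − 1.96 x 0.0441)/0.0433 = −0.84, so the chance of a significant result favouring the card is 20%.

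Over the 20% to 50% range the chance is 17% to 25% for a 5-point fall and 53% to 81% for a 10-point fall. Without bias it is 2.5% in that direction.

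**4. Precision of the randomised contrast.** Each side has 80 + 80 = 160 enrolled, or 64 + 64 = 128 after 20% loss. Half-width of the 95% interval = 1.96 x √(2p(1−p)/n):

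| Assumed risk p | n = 160 per side | n = 128 per side |
|---|---|---|
| 10% | 6.6 points | 7.4 points |
| 30% | 10.0 points | 11.2 points |
| 50% | 11.0 points | 12.3 points |

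**5. Power for 5 points on a yes/no outcome.** For a no-card risk of 10% to 50%, power falls from 33% to 12% at 128 per side and from 40% to 14% at 160 per side. The SD of 10% in Power calculation would give 98% at 128 per side, but a yes/no outcome has SD √(p(1−p)), which is 30% to 50% over this range. That is a separate matter and does not favour the 2007 comparison.

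**6. Interaction.** The card-by-leaflet interaction is a difference of differences over four groups. At p = 30% its half-width is 1.96 x √(4 x 0.21/80) = 20.1 points at 80 per group and 1.96 x √(4 x 0.21/64) = 22.5 points at 64. It can be reported, but only a large interaction would be visible.

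**The case against.** **A reader might infer that the plan rejects the factorial comparison.** The article does not say so. Intention to treat by allocated group, group-level analysis and adjustment for differences between groups all leave room for comparing randomised groups, and the exact contrast is commonly left to an analysis plan. This stands. What remains is that the one comparator actually named for the card is a poor one; that is a stated choice, not missing detail.

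**The baseline sentence may be meant for the whole programme.** It comes last under the card, after the 60% use-and-usefulness criterion, and does not say that only card patients are compared with 2007. General data collection and follow up gives the second record review a programme-level purpose. This is a fair reading, but the sentence sits under evaluation of the card and would have to be reworded to say so.

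**A reader might extend the point to the leaflet.** Intervention C, Evaluation, names no historical comparator, so the article does not support that.

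**A reader might infer that half the patients are thrown away.** Groups of 80 belong to the sizing in Power calculation. A comparison of card patients with 2007 would use about 160 of them, so the defect is confounding, not lost numbers.

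**Complications are not an outcome of question 2b.** True, but they are a primary outcome of the trial and the card's own evaluation section plans to compare them.

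**A reader might conclude that trust is asked of card holders only.** The wording points that way, but every patient is interviewed at two weeks and nothing assigns trust to the group-specific questions. It is plausible, not established.

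**The randomised contrast is not perfect.** The article concedes that patients sharing a room may expose each other to the interventions. The envelope is taken when a patient is asked to participate, so consent could depend on allocation. Both are limits, but neither brings in SBAR, calendar time or the 2007 case mix.

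**Conclusion.** The point holds for the card. The comparator named in Intervention B, Evaluation, cannot separate the card from SBAR, the leaflet, time and case mix, while a concurrent within-ward randomised contrast exists and is not named. Under the stated assumptions, a fall of 5 points from other causes would be taken for a card benefit in about one trial in four to six, and a fall of 10 points in more than half. These figures depend on the assumed 300 baseline records and 20% to 50% risk; the list of confounders does not.

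The randomised contrast removes these sources of bias but is not precise: about ±10 to 11 points at an assumed 30% risk, against a 5-point target. It should be presented as the right estimate with a wide interval, not as a well-powered test.

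**What to change.** - **Card:** name groups 2+4 v 1+3 as the comparison for complications and adverse events, adjusted for ward and leaflet.
- **Leaflet:** name groups 3+4 v 1+2, adjusted for ward and card, on events after discharge. Question 2c concerns these; in-hospital events would dilute the contrast.
- **Interaction:** report the card-by-leaflet interaction with its confidence interval.
- **2007 baseline:** reword the sentence in Intervention B so that this comparison is descriptive or refers to the whole programme, and state the differences in eligibility.
- **Question 2b:** put the same trust and error-signalling questions to all four randomised groups in the two-week interview that every patient already has.

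No extra patients or visits are needed; the cost is analysis wording and a few common interview items. The downside is that the pooled margins assume no large interaction, which this trial can check only roughly, and contamination between patients in the same room may pull the estimates towards no effect.

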#### Intervention C: Reducing avoidable harm after discharge (Research question 2c)

##### Aim

To provide the patient with information and to reduce avoidable harm after discharge, such as adverse medication events, pneumonia, urinary tract infections, wound infections, delirium, falls and pressure ulcers.

##### Background

The intervention consists of standardised information using an information leaflet with "bundles" for the patient after discharge. The concept of "bundles" was developed and tested by the Institute of Healthcare Improvement in Boston [40]. A bundle is a structured way of improving the processes of care and patient outcomes. It involves a small straightforward set of practices that have been shown to improve patient outcomes. The recommendations in the "bundles' for the period after discharge are evidence based best practices [41]. Bundles were originally developed for use by health care professionals, in our study we aim to adapt this concept for use by patients after discharge. The evidence based best practices will be reformulated to make them understandable and usable for patients and they will be printed into an information leaflet. The following topics will be described in the leaflet:

• Contact information;

• Exercise recommendations;

• Medication use;

• Problems with the operation wound;

• Thrombosis;

• Pressure wounds;

• Urinary tract infection;

• Fall prevention;

• Delirium.

##### Implementation

In the intervention wards 50% of the included patients will receive the leaflet with instructions. For each included patient a short questionnaire about the health status before discharge will be filled out to determine for which complications a patient may be at increased risk. The chapters concerning these complications are checked in the leaflet to indicate the most relevant information for each specific patient.

##### Evaluation

The use of the leaflet will be evaluated by asking the patient about the added value and the usability of the bundles during a short interview by telephone two weeks after discharge. We will consider the leaflet useful if 60% of the patients says they have used the leaflet and found it useful. The effect of the bundles will be evaluated during the telephone interview two weeks after discharge and by measuring avoidable harm (e.g. adverse medication events, urinary tract infections, wound infections, delirium, falls and pressure ulcers) within 6 months after discharge. The patient will be called again around 6 months after discharge to ask about any medical problems occurring after discharge and their recovery in the past six months. Also, the patient records of all included patients will be reviewed by experienced reviewers for additional information about possible complications and avoidable harm after discharge.

### Outcome measures

The primary outcome measures in this study are the incidence of complications and adverse events, mortality rate within six months after discharge and functional mobility six months after discharge. Secondary outcome measures are length of hospital stay, quality and completeness of information transfer and patient satisfaction with the instruments.

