### Aim and research questions

The aim of this randomised controlled trial (RCT) is to evaluate the effectiveness of a patient safety intervention programme for elderly hip fracture patients. Therefore, the following research questions will be addressed:

1. What is the nature and scale of adverse events and avoidable harm in the care chain for elderly hip fracture patients?

2. How is it, in the total care chain of elderly hip fracture patients, possible to reduce risks and unintended harm, and to ensure that complex care processes proceed more safely? This research question is divided into sub-questions for the three interventions:

a What is the effectiveness of the SBAR communication tool on unintended events and avoidable harm during hospital stay? (Intervention A)

b What is the effectiveness of a patient safety card with guidelines for patients and their families on signalling errors and patient trust in health care? (Intervention B)

c What is the effectiveness of evidence based bundles with regard to unintended events in the period after discharge? (Intervention C)

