The records will be reviewed by one reviewer and he determines whether complications, an adverse event or a near miss have occurred during the index admission to the hospital or the six months following the index admission using a paper based structured review form. This review form will be adapted from the Dutch Adverse Event Study [34,39] and adjusted and specified for this patient group. The review form starts with general characteristics of the admission and possible complications. Next, if the surgeon determines that an adverse event is present, the review will be continued with questions about the nature and impact, location and involved specialty, classification, preventability and causes of the adverse event. The last part of the review form will be about the clarity and completeness of information in the patient record for the transfers of the patient between the different wards and specialties within the hospital.

A random sample of 10% of the records will be independently reviewed by a second reviewer to assess the variation in the review process between reviewers.

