### Data analysis

The data will be analysed using Stata 10.1 for Windows. During the data collection regular data checks (identify out-of-range answers, inconsistent responses and missing data) will be performed.

In the evaluation of the effectiveness of the intervention programme all analyses will be performed at patient and group level. The data will be analysed using the intention-to-treat principle. This means that patients will remain in the group to which they were randomly allocated at baseline. The patient characteristics will be compared for all groups and, if necessary, we will correct for differences.

The determination of complications is based on the complication registration of the Dutch Society of Medical Specialists (in Dutch: Orde van Medisch Specialisten). The determination of adverse events is based on three criteria; 1) an unintended (physical and/or mental) injury which 2) results in temporary or permanent disability, death or prolongation of hospital stay, and is 3) caused by health care management rather than the patient's disease. To determine whether the injury is caused by health care a six-point scale will be used, causation scores of 4-6 will be classified as adverse events. The preventability of the adverse events will also be measured on a six-point scale, scores of 4-6 will be classified as preventable adverse events. The incidence and mean number of complications and adverse events will be calculated.

The inter-rater reliability of the review process will be expressed as a kappa statistic. This kappa statistic will be calculated for the determination of the presence or absence of complications and adverse events. The records from the reliability study will be used for this analysis, they represent up to 10% of all reviewed patient records.

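### The primary mortality outcome is counted from discharge, so read literally it omits deaths during the index admission, when SBAR and the patient safety card act

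*Protocol article*

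**What the plan says.** The section Outcome measures names as primary outcomes the incidence of complications and adverse events, together with "mortality rate within six months after discharge and functional mobility six months after discharge". The abstract defines mortality in the same words. No section gives another starting point for mortality or says how a death before discharge is handled.

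Other parts of the article bear on this choice:

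- **Entry to the trial** (Participants): "Patients will be recruited as quickly as possible after admission to the hospital".
- **SBAR** (Aim and research questions, question 2a): "What is the effectiveness of the SBAR communication tool on unintended events and avoidable harm during hospital stay".
- **Patient safety card** (Intervention B, Implementation): "The card will be given to the patients during the hospital admission with a short instruction on how to use the card".
- **Care chain under study** (Baseline measurement, Method): "from the moment that the patient is brought into the emergency department until six months after discharge from the hospital".
- **Window for complications, adverse events and near misses** (same section): the reviewer judges whether they "have occurred during the index admission to the hospital or the six months following the index admission". General data collection and follow up applies identical methods to the trial patients.

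**The concern.** Included patients are at risk of dying in hospital from the day they enter, and two of the three interventions are at work in that period. A rate that starts at discharge has no evident place for a patient who is never discharged alive.

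There are two consequences. A death that better ward communication or a better-informed patient might have prevented does not register in the primary mortality result. And the groups are compared among survivors to discharge, a subset formed after inclusion. If an intervention changes who survives the stay, those survivors need no longer be comparable between groups.

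Mortality is also out of step with the article's own framing, since both the care chain and the window for complications and adverse events take in the index admission.

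**Working it through.** **The plan's own figures.** No mortality rate or mortality sample size is planned, so there is none to reproduce. The group size used below comes from the power calculation for complications, which does reproduce. With a difference of 5%, SD 10%, two-sided alpha 0.05 (sidedness assumed) and 80% power, n = 2 × (1.96 + 0.84)² × (0.10/0.05)² gives 63 per group by the normal approximation and 64 by the t-test. Then 64/(1 − 0.20) = 80.

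**Which contrasts are affected.**

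- SBAR: all four randomised groups receive it, so an SBAR effect on in-hospital death could show only against the control ward, which is not randomised.
- Card: given to half of the intervention-ward patients during admission. This contrast is randomised and is affected.
- Leaflet: aimed at harm after discharge, so a window opening at discharge suits it.

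**Deaths left out.** The only mortality figure in the article is 14-36% at one year (Background). As an assumption, take in-hospital mortality of 3-6%:

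- 80 × 0.03 = 2.4 and 80 × 0.06 = 4.8, so about 2-5 deaths per group.

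This is a count of deaths not seen, not a difference between groups.

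**What the outcome can miss.** Let h be the in-hospital risk and q the six-month risk after discharge in survivors. The risk from inclusion to six months after discharge is h + (1 − h) × q. All rates are assumed, and control is listed first.

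| h | q | Risk from inclusion | Reduction counted from inclusion | Reduction counted from discharge |
|---|---|---|---|---|
| 4% vs 2% | 12% vs 12% | 15.5% vs 13.8% | 1.8 points | 0 |
| 6% vs 3% | 12% vs 12% | 17.3% vs 14.6% | 2.6 points | 0 |
| 8% vs 4% | 12% vs 12% | 19.0% vs 15.5% | 3.5 points | 0 |
| 6% vs 3% | 12% vs 14% | 17.3% vs 16.6% | 0.7 points | −2 points |

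Second row in full: 0.06 + 0.94 × 0.12 = 0.1728 and 0.03 + 0.97 × 0.12 = 0.1464, a difference of 2.6 points. In the last row the extra survivors are assumed to be frailer: 0.03 + 0.97 × 0.14 = 0.1658. Total mortality is then lower, yet the discharge-based outcome points to harm.

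**Moving the start of the window.** With a constant hazard λ = −ln(1 − annual risk)/365, the risk over 182 days is 7.2% (from 14% a year) or 20.0% (from 36%). Two to five further days add about 0.1 to 0.5 points. This is minor beside the omitted deaths.

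**The case against.** The best defence is that the phrase marks only the end of follow-up. The care chain runs from the emergency department to six months after discharge, and the mortality outcome may have been meant to share that window. No denominator for mortality is given, so the exclusion of in-hospital deaths follows from the literal wording and is not announced. This stands as a reason to call it a literal reading. It does not remove the problem, because the abstract and the outcome section both name discharge as the only reference point.

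In-hospital deaths are also not wholly lost. Under the definitions in Table 1, a death caused by health care management is an adverse event, and an unwanted event with irreparable harm can count as a complication. That stands too. But such deaths are merged with lesser events, and neither outcome amounts to all-cause mortality.

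Several stronger readings are tempting, and the documents do not support them:

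- A reader might infer a contradiction with the sentence "The data will be analysed using the intention-to-treat principle". The Data analysis section explains the term only as keeping patients in their allocated group. It does not say who enters each denominator, so that wording is not breached.
- Since length of stay is a secondary outcome ("Secondary outcome measures are length of hospital stay, quality and completeness of information transfer and patient satisfaction with the instruments"), a reader might infer that treatment shifts the start of the window. It could, but no effect is shown, and a shift of a few days matters little.
- A reader might want to state what share of all deaths is missed. The article gives neither an in-hospital nor a six-month rate. Its one-year range may not carry over to patients who must be operated on and able to consent, with dementia excluded.
- A reader might extend the point to how deaths are scored in six-month mobility. That is a separate and debatable choice of estimand.

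**Conclusion.** The point holds as a badly chosen window for a primary outcome. As written, mortality counts from discharge, omits index-admission deaths and is restricted to patients discharged alive, although inclusion, SBAR and the card all come earlier. It affects the randomised card contrast and the non-randomised programme contrast, but not the rationale for the leaflet.

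Its size rests on assumption. At 3-6% in-hospital mortality, about 2-5 deaths per group of 80 would be uncounted. The illustrations show that a real in-hospital benefit can go unseen or even be reversed; they do not show that this will happen. If the intention was to include in-hospital deaths, the defect is in the wording and the same change settles it.

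**What to change.** Define the primary mortality outcome as death from any cause from inclusion to a fixed six months, in all included patients, with deaths during the index admission counted. Report in-hospital and post-discharge deaths separately, so that the period relevant to the leaflet remains visible.

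The cost is a change to the outcome definition, in the abstract and in Outcome measures. The hospital records of included patients are already to be reviewed, and follow-up to six months after discharge necessarily covers six months from inclusion. The date of death must be recorded so that each death can be placed in the window. One small weakness remains: deaths outside hospital depend on the six-month contact, as they do under the present definition.
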